### Sample size

It is our hypothesis that computer-navigated MIS will lead to better recovery during the early postoperative period (3 months), and at least as good at 6 months postoperatively. In order to detect a difference of 0.254 in the proportion of subjects with normal gait after 3 months of follow-up with 80% power at a significance level of 0.05 in a one-sided test of a difference between two proportions, two groups of 50 subjects are required. With an expected dropout rate of 10%, a total of 110 patients is needed. At 6 months, the effect of MIS and conventional THA technique on gait (limping) will be compared in a non-inferiority setting. To establish non-inferiority, the lower bound of the 95% confidence interval of the difference between the two treatment groups will be compared with a non-inferiority margin delta. If the whole confidence interval of the difference between the two treatments is smaller than the non-inferiority margin delta, non-inferiority is established. The non-inferiority margin delta is chosen in this study at a value of 0.10, indicating that a difference in proportion of subjects with a normal gait of 0.10 is considered clinically equivalent. To deduce non-inferiority with 80% power at a significance level of 0.05 with expected proportions of subjects with normal gait of 0.95, using a non-inferiority margin delta of 0.10, two groups of 60 subjects are required. With an expected dropout rate of 10%, a total of 132 patients is needed.

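### The 10% dropout allowance is added to the required number instead of being taken from the enrolled number, so totals of 110 and 132 fall just short of 100 and 120 evaluable patients

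*Protocol article*

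**What the plan says.** The Sample size section of the protocol article makes two calculations and applies a dropout allowance to each.

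- 3 months, superiority on the proportion with normal gait: "two groups of 50 subjects are required. With an expected dropout rate of 10%, a total of 110 patients is needed".
- 6 months, non-inferiority on the same outcome, for which 60 per group are called for: "With an expected dropout rate of 10%, a total of 132 patients is needed".

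The section does not say how the allowance was computed, and nothing elsewhere in the article explains or corrects the two totals. The larger total, 132, is the one that would govern enrolment.

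**The concern.** A dropout rate describes the fraction of enrolled patients who will not supply the outcome. To end with a required number, that number has to be divided by one minus the rate. Both totals look as if the required number had simply been increased by 10%, which always gives too few. If so, a trial that recruits exactly to target and loses exactly the expected share finishes below the group sizes the section says it needs. At stake is the internal consistency of the enrolment target: required size, dropout rate and total cannot all be right as printed.

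**Working it through.** **Inputs, all from the Sample size section:** 50 per group (100 in total) at 3 months; 60 per group (120 in total) at 6 months; 10% dropout; stated totals 110 and 132; for non-inferiority, expected proportions of 0.95 in both groups, margin 0.10, significance level 0.05, 80% power.

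**1. Reproducing the stated totals.** Required number × (1 + 0.10):

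- 100 × 1.10 = 110
- 120 × 1.10 = 132

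Both match exactly. The method is therefore inferred, though with little doubt. The next step does not depend on the inference.

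**2. What the stated totals deliver at 10% dropout.**

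| Comparison | Stated total | × 0.90 | Per group | Required in total | Shortfall |
|---|---|---|---|---|---|
| 3 months | 110 | 99.0 | 49.5 | 100 | 1.0 |
| 6 months | 132 | 118.8 | 59.4 | 120 | 1.2 |

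**3. Dropout the totals can absorb.** 1 − 100/110 = 1 − 120/132 = 9.1%.

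**4. Totals consistent with 10%.** Required number ÷ (1 − 0.10):

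- 50/0.90 = 55.6, so 56 per group and 112 in total (112 × 0.90 = 100.8)
- 60/0.90 = 66.7, so 67 per group and 134 in total (134 × 0.90 = 120.6)

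Each is two patients above the stated total.

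**5. Effect on non-inferiority power.** The section names no formula, so the usual unpooled normal approximation is assumed, at one-sided 0.05 and without clustering.

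- Required size: n = (1.645 + 0.842)² × 2 × 0.95 × 0.05 / 0.10² = 58.7 or 58.8 depending on rounding of the quantiles, so 59 per group. This agrees with the stated 60.
- Power = Φ(0.10 / √(2 × 0.95 × 0.05 / n) − 1.645)
- n = 60: Φ(2.513 − 1.645) = 80.7%
- n = 59.4: Φ(2.501 − 1.645) = 80.4%

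**6. Effect on superiority power at 3 months.** The section gives the difference (0.254) but not the two proportions. Taking the lower proportion anywhere from 0.30 to 0.74 as an assumption, with a one-sided 0.05 test and no continuity correction, going from 50 to 49.5 per group costs less than 0.4 percentage points. Power stays at about 81.9% or more throughout. This loss would arise only if enrolment stopped at 110.

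**The case against.** The best case against the point is that it changes nothing of substance.

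- **Power is still met.** On the stated inputs at one-sided 0.05, 59 per group is enough, and 59.4 remain on average. What is missed is the rounded 60, not the 80% target. This stands, and it is why the point is minor.
- **The 3-month total is redundant.** If 132 are enrolled, about 118 remain against the 100 needed at 3 months. This also stands: correcting 110 is a matter of consistency only.
- **10% is itself a round guess.** The gap between 9.1% and 10% is well within its uncertainty, and adding 10% is a familiar rough allowance. That is fair as to consequence, but the section states an expected rate and a total that disagree, and rounding cannot turn 133.3 into 132.
- **134 is right only if 60 is right.** The section judges non-inferiority by a 95% confidence interval. If that interval is two-sided, the same formula at one-sided 0.025 needs 75 per group, and 60 gives about 71% power. The Study design section specifies cluster randomization, while the sample size calculation mentions no allowance for it. These are separate questions about the base number. They make the corrected totals conditional, and they mean the one-patient cushion at one-sided 0.05 should not be relied on to dismiss the discrepancy.

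**Conclusion.** The point holds. At the dropout rate the article expects, neither total yields the evaluable number it calls for: 99 instead of 100, and 118.8 instead of 120. The error is one to two patients and about 0.3 percentage points of non-inferiority power, with 80% still reached under one-sided 0.05 and no clustering. The shortfall follows from the printed figures alone; the power figures rest on the normal approximation and those two conditions. It is a minor correction to a stated figure, and no conclusion of the trial turns on it.

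**What to change.** If 50 and 60 per group are retained, either:

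- replace 110 by 112 and 132 by 134, which costs two more patients on the total that governs enrolment; or
- keep 110 and 132 and state the allowance as 9% (110 × 0.91 = 100.1; 132 × 0.91 = 120.1), which costs only a wording change.

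In either case, add a few words saying that the required number was divided by one minus the dropout rate. If the base group sizes are revised for another reason, apply the same division to the new numbers.

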### Statistical analysis

All statistical analyses will be computed using the Statistical Package for the Social Sciences (SPSS, Inc., Version 12.0, 2003, Chicago). Descriptive statistics will be used to describe both research groups. Analysis of variance (ANOVA) and chi-square procedures will be used to evaluate between-group differences at baseline. Random effect models will be applied for longitudinal analyses. In order to enable statistical conclusions on differences in (skewed distribution of) costs between groups during the study, nonparametric confidence intervals will be constructed based on results of bootstrap analyses. For all test procedures, a probability value of less than 0.05 will be considered as statistically significant.

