## Methods/design

### Study design

A cluster randomized controlled trial will be conducted. Patients will be stratified into 3 groups based on the Charnley classification, by means of which total hip arthroplasty patients can be subdivided by degree of comorbidity affecting the function of walking. The Charnley classification recognizes three categories. Category A denotes patients with only one hip involved, in whom no other condition interferes with walking. Category B denotes patients with both hips involved but the rest of the body normal and therefore not responsible for any defect in walking. Category C denotes patients with some factors contributing to failure to achieve normal locomotion, such as polyarthritis or rheumatoid arthritis, or cardiovascular or respiratory disability [16]. By using this stratification, the influence of factors other than the THA affecting normal walking will be accounted for.

Within the strata, patients will be randomly allocated to have computer-navigated MIS or the conventional THA procedure by means of cluster randomization to avoid interaction between both patient groups. The random allocation sequence will be computer-generated by an independent planner of the Medical Assessment Office of University Medical Center Groningen (UMCG). The study design, procedures and informed consent are approved by the Medical Ethics Committee of UMCG.

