### Measurements

In this study, recovery is operationalized as the proportion of subjects with normal gait (no limping during walking) and as the self-reported functional status and health-related quality of life. Measurements will take place preoperatively (day of admission) and perioperatively, and 6 weeks and 3 and 6 months postoperatively. The amount of limping and self-reported functional status and health-related quality of life will be assessed preoperatively as well as postoperatively. Perioperative complications will be registered. Evaluation of prosthesis positioning will take place 6 weeks and 6 months postoperatively. The economic evaluation will focus on differences in costs between computer-navigated MIS and conventional THA technique. The evaluation will be performed from a societal perspective; costs within and outside the healthcare sector will be registered over a period of 6 months. Demographic data, diagnosis, height, weight and BMI, and ASA and Charnley classifications will also be recorded preoperatively.

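### The analysis text does not carry the Charnley strata or the preoperative values into the gait comparisons and outcome models, and plans baseline significance tests that cannot correct imbalance

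*Protocol article*

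**What the plan says.** All references are to the protocol article.

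- **Study design.** "Patients will be stratified into 3 groups based on the Charnley classification". Allocation respects these groups: "Within the strata, patients will be randomly allocated to have computer-navigated MIS or the conventional THA procedure by means of cluster randomization". The stated benefit is: "By using this stratification, the influence of factors other than the THA affecting normal walking will be accounted for".
- **Measurements.** "The amount of limping and self-reported functional status and health-related quality of life will be assessed preoperatively as well as postoperatively". Further baseline variables are listed: "Demographic data, diagnosis, height, weight and BMI, and ASA and Charnley classifications will also be recorded preoperatively".
- **Sample size.** The 3-month gait comparison is described as a one-sided test of two proportions. The 6-month comparison is a 95% confidence interval for the difference between the two groups, set against a margin of 0.10. Neither description mentions strata or baseline gait.
- **Statistical analysis.** "Analysis of variance (ANOVA) and chi-square procedures will be used to evaluate between-group differences at baseline". Then: "Random effect models will be applied for longitudinal analyses". No fixed effect, covariate or stratum term is named. The threshold is common to everything: "For all test procedures, a probability value of less than 0.05 will be considered as statistically significant".

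**The concern.** Charnley class was chosen as the stratification factor because it reflects conditions that affect walking, and walking is the outcome that sizes the trial. Stratified allocation aims to balance the class between arms. That balance reduces the true sampling variability of the difference, but a crude two-proportion standard error does not see the reduction. The interval is then wider than it need be and the test is conservative. The benefit of stratifying is paid for in the design and only partly collected in the analysis.

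The planned baseline tests do not fill this gap. Under proper randomisation any baseline difference is due to chance, so the tests address a null hypothesis already known to be true. A significant result does not remove an imbalance, and a non-significant one does not show that an imbalance is harmless to the outcome comparison.

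At stake is some precision on gait, and possibly more on WOMAC, SF-36 and EuroQol 5D, using data the trial already has. There is also a risk that chance p-values at baseline invite ad hoc adjustment.

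**Working it through.** **1. The plan's own sample sizes.** These are context only; the point does not depend on them.

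- *6 months:* n per arm = (1.645 + 0.842)² × 2 × 0.95 × 0.05 / 0.10² = 58.8, so 59 against the stated 60 (one-sided 0.05, 80% power).
- *3 months:* the control proportion behind the difference of 0.254 is not given. Scanning it from 0.25 to 0.74 gives at most 47 per arm without continuity correction and 29 to 55 with it. The stated 50 is therefore attainable but cannot be tied to one pair of rates.

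**2. Effect of leaving balanced strata out of the gait comparison.** From the article: three strata, 50 per arm, one-sided 0.05, difference 0.254. Assumed, because the article gives neither: a Charnley A/B/C mix of 50/30/20%, and the normal-gait rates in the table. Strata are taken as exactly balanced and patients as independent.

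*Variance check.* With weights w and stratum rates p, the crude test uses P(1 − P), where P = Σwp. The variance that applies under balanced strata is Σw·p(1 − p). The crude interval is too wide by the square root of their ratio, and the true one-sided error is the normal tail beyond 1.645 times that factor.

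| Rates A/B/C | P(1 − P) | Σw·p(1 − p) | Width factor | Implied error |
|---|---|---|---|---|
| 0.6/0.5/0.3 | 0.51 × 0.49 = 0.2499 | 0.120 + 0.075 + 0.042 = 0.237 | 1.03 | 0.046 |
| 0.7/0.5/0.2 | 0.54 × 0.46 = 0.2484 | 0.105 + 0.075 + 0.032 = 0.212 | 1.08 | 0.037 |
| 0.7/0.45/0.1 | 0.505 × 0.495 = 0.2500 | 0.105 + 0.074 + 0.018 = 0.197 | 1.13 | 0.032 |

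*Simulation (40,000 runs per setting).* Crude two-proportion test against a Mantel-Haenszel stratified test; the power columns add 0.254 in every stratum.

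| Rates A/B/C | Type I, crude | Type I, stratified | Power, crude | Power, stratified |
|---|---|---|---|---|
| 0.5/0.5/0.5 | 0.045 | 0.045 | 0.853 | 0.846 |
| 0.6/0.5/0.3 | 0.042 | 0.050 | 0.866 | 0.874 |
| 0.7/0.5/0.2 | 0.035 | 0.053 | 0.896 | 0.920 |
| 0.7/0.45/0.1 | 0.028 | 0.050 | 0.892 | 0.931 |

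The simulation and the variance check agree in direction and roughly in size. When gait does not differ by class, stratifying costs almost nothing (0.846 against 0.853). When it does differ, the crude test falls below its nominal level and loses 0.8, 2.4 and 3.9 points of power in the three settings.

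The 6-month comparison was not simulated. With 95% expected to walk normally in both arms, there is less room for gait to differ by class, so a smaller effect is likely there.

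**3. Continuous outcomes.** Adjusting a follow-up score for its preoperative value leaves residual variance 1 − r². For assumed r = 0.3, 0.5 and 0.6 this is 0.91, 0.75 and 0.64. At r = 0.5, 1/0.75 = 1.33, equivalent to about 33% more patients than an analysis of the follow-up score alone.

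**4. Baseline tests.** The chance of at least one p < 0.05 among k independent true nulls is 1 − 0.95^k: 0.34 for k = 8, 0.40 for k = 10 and 0.54 for k = 15. The number of variables tested is assumed. The article lists demographics, diagnosis, height, weight, BMI, ASA, Charnley class and the preoperative outcome measures, so counts of this order are plausible.

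**The case against.** The strongest reply is that the article is silent here and does not exclude anything. Random effect models can carry a Charnley term and baseline values, and a condensed article commonly leaves its covariate list to a fuller document. The preoperative measurement is one of the repeated occasions, so a longitudinal model may already use it. The Study design section credits the accounting to stratified allocation, which does aim to balance Charnley class. No stated rule lets the baseline tests drive the outcome analysis. Surgical time, blood loss, transfusion and incision length have no preoperative value to adjust for.

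Most of this stands, and it rules out several stronger readings that a reader might infer:

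- *That the plan excludes strata and baseline values, or tests baseline differences in place of adjusting.* The tests and the models are listed side by side, and nothing says that one replaces the other.
- *That the gait comparison would be biased.* Chance imbalance under random allocation adds variance; it is not systematic bias.
- *That imbalance is likelier because clusters are few.* The article gives neither the cluster unit nor the number of clusters, so how well the strata balance cannot be judged either way.
- *That a gain of about 33% applies to the trial's main comparison.* That figure rests on an assumed correlation, is measured against an analysis that discards baseline, and does not concern the gait proportion.

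The reply does not remove two things that are written down. The gait comparisons, including the 6-month decision rule, are described as plain two-group differences although allocation is stratified. And baseline significance tests are explicitly planned.

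**Conclusion.** The point holds as a moderate and inexpensive improvement. As described, the gait comparison would be valid but somewhat conservative when gait differs by Charnley class: an interval about 3% to 13% too wide, type I error about 0.03 to 0.04 against 0.05, and 0 to 4 points of power lost. These figures rest on an assumed class mix, assumed stratum rates, exactly balanced strata and independent patients. If gait does not vary by class, nothing is lost. For continuous outcomes the gain depends on a baseline correlation that the article does not give, and on how far the random effect models already use the preoperative occasion.

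The statement that stratification accounts for other walking factors is not contradicted by the article. It is only partly carried through, because the described gait analysis does not reflect the stratified design. The baseline tests are a poor stated choice, but their direct consequence is small.

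**What to change.** In the Statistical analysis section, or in the analysis plan if one exists:

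1. Estimate the 3- and 6-month differences in the proportion with normal gait stratified by Charnley class (for example, a Mantel-Haenszel risk difference) or adjusted for it, and use that interval for the 6-month non-inferiority decision.
2. Include Charnley class and the preoperative value of the outcome, where one exists, in the random effect models. Fix this in advance, whatever the baseline data show.
3. Present baseline data descriptively by arm and delete the ANOVA and chi-square tests of baseline differences.

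This costs wording only. It uses data already collected and changes no stated sample size. How clustering enters these analyses is a separate issue and should be settled separately.

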## Discussion

Over the last few years, MIS has become a widely used technique for THA. Several authors [5,6,32] have concluded that MIS is a safe and reproducible procedure. Chimento et al. [6] executed a randomized prospective study comparing MIS to a standard approach. There was no difference between the groups in number of patients being able to achieve rehabilitation milestones. However, patients who underwent MIS demonstrated decreased blood loss and limped less 6 weeks postoperatively, indicating a quicker return to a more normal gait. An objective gait analysis was not performed though. In a retrospective cohort study, Woolson et al. [33] attempted to determine whether there was a difference in surgical parameters and component positioning of MIS compared to a standard THA technique. The results showed no differences with respect to surgical parameters. It was concluded that there were no benefits associated with MIS except for a smaller scar. However, more malpositions of the acetabular and femoral components were seen in the MIS group. Malpositioning is a potential complication of MIS due to poorer operative visualization. Computer navigation can be a preventive tool as it permits accurate orientation and fixation of the prosthesis without the need for visualization of bony landmarks. Computer navigation has proved to decrease inaccuracies in prosthesis placement by means of conventional THA technique [9-11].

Wixson and MacDonald [12] found more reproducible acetabular component placement in a series of computer-navigated MIS as compared to a cohort of a conventional THA technique. They concluded that using MIS in combination with computer navigation can improve the accuracy of component placement. DiGioia and colleagues [7] compared MIS and conventional surgery, both with the help of computer navigation. At 3 months, MIS patients had significantly better results in limping and stair-climbing, and at 6 months in limping, walking and stair-climbing as determined with the Harris hip score. They used a matched control group and patients were not randomized.

The literature lacks well-designed studies that provide objective evidence to conclude that computer-navigated MIS is superior to a conventional procedure for THA. Additionally, there are conflicting reports on the cost advantages of (computer-navigated) MIS over conventional THA techniques [13-15].

Purpose of the study presented in this article is to compare (cost) effectiveness of two THA techniques: computer-navigated MIS and a conventional technique. Since computer-navigated MIS is less invasive to muscles and skin, advantages are expected in the early postoperative phase in terms of a quicker recovery. We also hypothesize that it leads to fewer perioperative complications, better prosthesis positioning and cost savings. The results of this study will be presented as soon as they become available.
